**GENERAL INFORMATION**

This document describes the TILT trial and provides information about procedures for entering patients into it. The protocol should not be used as an aide-memoire or guide for the treatment of other patients. Every care was taken in the creation of this document, but corrections or amendments may be necessary.

**COMPLIANCE**

The trial will be conducted in compliance with the protocol, Research Governance Framework, Data Protection Act and other guidelines as appropriate.

**FUNDING SOURCE**

This trial has been funded by a National Institute of Health Research (NIHR) Doctoral Research Fellowship (DRF) awarded to [name] (reference DRF-2016-09-065).

# ABBREVIATIONS

°C Degrees centigrade

AE Adverse event

AR Adverse reaction

BCG Bacille Calmette Guerin

CI Chief Investigator

CRP C reactive protein

CT Computed tomography

CXR Chest radiograph

DMP Data Management Plan

ECOG Eastern Co-operative Oncology Group

EoT End of trial

EQ-5D-5L EuroQol 5D health questionnaire

eCRF Electronic case report form

FBC Full blood count

GCP Good Clinical Practice

GMC General Medical Council

GP General Practitioner

IMP Investigational medicinal product

IPC Indwelling pleural catheter

LFT Liver function tests

MDT Multidisciplinary team

MHRA Medicines and Healthcare Products Regulatory Agency

Ml Millilitres

MPE Malignant pleural effusion

MPM Malignant pleural mesothelioma

NBT North Bristol NHS Trust

NHS National Health Service

OS Overall survival

PI Principal Investigator

PFSR Progression-free survival rates

PROMs Patient-reported outcome measures

PS Performance status

QoL Quality of life

R&I North Bristol NHS Trust Research & Innovation Department

RCT Randomised controlled trial

REC Research Ethics Committee

RSI Reference Safety Information

SAE Serious adverse event

SAR Serious adverse reaction

SmPC Summary of Product Characteristics

SUSAR Suspected unexpected serious adverse reaction

TSC Trial steering committee

TSP Trial specific procedure

TUS Thoracic ultrasound scan

TWIC Trial within a cohort

U&E Urea and electrolytes

VAS Visual analogue scale

WHO World Health Organisation

YTU York Trials Unit, a UKCRC-registered, NIHR Clinical Trial Unit

# TRIAL OVERVIEW

## Plain English summary

Mesothelioma is an aggressive cancer that affects the outside lining of the lung, called the pleura. It is incurable, and there is only one effective chemotherapy treatment available. This chemotherapy extends life by just three months on average. It is crucial that we find new treatment options that can be offered to people with this disease.

There are lots of new treatments being developed for other cancers that focus on the immune system. A healthy immune system is able to identify and attack cancer cells within the body. However, mesothelioma hides from the immune system by reducing the number of protective immune cells in and around the pleura. People with mesothelioma who can overcome this and maintain lots of immune cells in the lung lining seem to live longer.

We have noticed that patients with mesothelioma live longer after having an infection in the pleura. We think this is because the infection “wakes up” the immune system that was suppressed by the mesothelioma. Immune cells move to the lung lining to attack the infection, and are able to attack the mesothelioma at the same time.

Our research aims to use two different bacterial agents to mimic infection and stimulate the immune system to attack the mesothelioma. The two bacteria are OK432, an inactivated, “dead” bacteria and BCG, a weakened version of the tuberculosis bacteria, currently used as a vaccine. We want to investigate whether either of these bacterial agents could help people live longer with mesothelioma. We will use a research design that aims to copy real life clinical care (called the ‘trial within a cohort’ design), to see whether it can be used in larger mesothelioma trials.

We are currently running a study called ASSESS-meso in which patients with mesothelioma undergo regular assessments, blood tests and CT scans. Everyone in ASSESS-meso has agreed for their information to be used to identify whether they are suitable for other research trials, and to be chosen on a random basis to be invited to join those trials. From ASSESS-meso we will identify 24 people who are suitable to join TILT, and will randomly choose 16 of those people to receive either OK432 or BCG. These people will receive a single dose of OK432 or BCG, delivered directly into the pleura via an indwelling catheter. The rest of the participants in ASSESS-meso won’t be told about the trial or the bacterial agents, because in real-life, doctors only tell patients about treatments if and when they are going to receive them, and not if they are not going to receive them. This prevents people becoming disappointed or disheartened with their treatment.

All participants will be followed up with the same tests. Participants who are not selected to receive OK432 or BCG will act as a comparison group for the people who do, having given their consent for their information to be used in this way when they first joined ASSESS-meso. At the end of the TILT trial we will assess various practical issues relating to the trial, e.g. how long it took to recruit participants, how many people agreed to receive OK432 or BCG and how many people completed the trial. At the end of the trial we will also interview some of the participants and their relatives to ask what it was like to participate in the trial, whether they had any problems with it, and what could be done differently in future. We hope to gain insight into people’s experiences of the trial that will help us make future trials acceptable and attractive to participants.

## Abstract

*Background*

Malignant pleural mesothelioma (MPM) is an aggressive cancer of the lung lining. It is incurable, with median survival less than 1 year from diagnosis^1-7^. Chemotherapy extends survival by 2.8 months, but is not suitable for everyone^1 2 4^. The UK has the highest mortality rates for MPM worldwide, with 2535 people dying from it in 2012^2^. Incidence is rising, and is predicted to peak in the next decade^1-3^.

MPM is an attractive target for immunotherapy as the tumour evades the immune response that usually inhibits tumour growth^8-11^. MPM suppresses populations of protective T cells in the pleura^10-13^. The ability to overcome this is associated with longer survival^12-15^, and drugs that stimulate T cell activity are currently undergoing clinical trials^16-18^.

T cells are stimulated by bacteria. Observational studies report enhanced survival in patients with lung cancer and pleural infection^19-22^. A similar phenomenon has been reported in a series of patients with pleural infection and malignant effusions, in which patients with MPM and pleural infection lived over a year longer than non-infected patients^23^. Historically, intra-pleural bacteria have been used as pleurodesis agents, with some demonstrating concomitant, anti-tumour activity^24-34^. Attenuated bacterial agents have been shown to control pleural fluid and prolong survival in malignant pleural effusions secondary to lung cancer^35-39^. In MPM, mice injected with staphylococcus enterotoxin demonstrated florid T cell responses in association with reduced tumour growth^40^.

This research will investigate two bacterial immunotherapy agents, OK432 and BCG. OK432 is a penicillin and heat-treated, lyophilized mixture of group A Streptococcus pyogenes that induced lymphocyte-mediated tumour killing in pleural fluid in vitro, controlled malignant pleural effusions in vivo and improved survival in lung cancer^35-37^. BCG, an attenuated, low-virulence mycobacterial strain has been used intra-thoracically following resection of lung tumours and is used intravesically in non-invasive bladder cancer [refs]

*Study design*

This project will investigate intra-pleural bacterial immunotherapy in MPM using an innovative trial design, the Trial within a Cohort (TwiC)^41^. Participants will be recruited from an existing observational cohort, consisting of regular clinical and radiological monitoring (the ASSESS-meso study). From ASSESS-meso, 8 eligible participants will be randomly selected for either the OK432 or BCG arm of the trial. OK432 or BCG will be delivered intra-pleurally as a single dose via an indwelling catheter. Outcome data will be compared with control participants from ASSESS-meso. Qualitative interview will be undertaken to assess acceptability of the methodology to participants.

*Aims*

The aims of this research are:

- To assess the feasibility and acceptability of the TwiC methodology
- To explore the role of intra-pleural bacterial immunotherapy in people with MPM
- To answer the question “Is it feasible to undertake a three-armed TwiC of intra-pleural immunotherapy in MPM and is it acceptable to participants and relatives?”

If feasibility is demonstrated, results will inform the design of a full-scale TwiC of intra-pleural bacterial immunotherapy using one or both agents from this study, depending on results.

## Study design

This is a multi-centre feasibility study for a single-blind, randomised, three-armed trial of intra-pleural bacterial immunotherapy in people with mesothelioma, based on the trial within a cohort design.

Patients with mesothelioma will be invited to participate in a longitudinal observational cohort study, consisting of pleural fluid monitoring, patient-reported outcome measurements, chest radiography (CXR) and blood tests (the ASSESS-meso study). Eligible patients will be identified from the cohort and randomly allocated to receive a single dose of either intra-pleural OK432 or intra-pleural BCG, or to remain in the cohort as a control. Identification of eligible participants will continue until 8 participants have been randomly selected to receive OK432 or BCG. Randomisation will be undertaken by a centralised, concealed computerised system with minimisation by tumour sub-type and WHO/ECOG performance status (PS). Participants selected to receive bacterial immunotherapy will receive it via an indwelling pleural catheter (IPC), on an unblinded basis. Participants who decline to receive OK432 or BCG following random selection will continue to undergo observational follow up, and their data will be collected as part of the feasibility outcomes.

Participants who are not selected to receive bacterial immunotherapy will continue longitudinal assessments as part of ASSESS-meso, blinded to the existence of the OK432 and BCG arms. This is consistent with real-life clinical care, wherein patients are told about treatments as and when they are going to receive them.

The primary outcome measure is feasibility. The trial will be deemed feasible if the following criteria are met:

- Recruitment rates to time & target >66%, i.e. 8 participants randomised in 12 month recruitment window, or 12 participants in 18 months.
- Attrition rate of <20% (nb this relates solely to attrition due to loss to follow up or participant withdrawal, it does not include attrition due to participant death)
- Data completeness rates >90%

In addition, data will be collected on specific elements of the TwiC methodology to explore the acceptability of the trial design to participants. These will include:

- Acceptance rates for intra-pleural OK432/BCG following random selection
- Number of control participants who were aware of the intervention arm
- Collection of data on participants who decline any element of the trial
- Qualitative interviews with participants and their relatives to explore the acceptability of trial processes.

Secondary outcome measures will collect exploratory data on the clinical efficacy of OK432 and BCG. They will include:

- Tumour response, based on CT appearances at baseline and 3 months, assessed using modified RECIST^42^
- Overall survival (OS), defined as time between date of diagnosis with MPM to date of death, censored at the end of the trial (EoT)
- Progression-free survival rates (PFSR) at 3 months
- Patient-reported chest pain and breathlessness, measured on visual analogue scales (VAS)
- Patient-reported quality of life, measured using the EQ-5D-5L health questionnaire
- Pleurodesis rates, defined as pleural fluid drainage of less than 50ml on 3 consecutive occasions, with <25% opacification on CXR or <250ml pleural fluid on thoracic ultrasound scanning (TUS)
- Adverse events
- Biomarker response assessed using serial serum mesothelin levels.

Following completion of the trial, participants will return to follow up within ASSESS-meso cohort study until death or withdrawal from the cohort. This will yield additional data over time, and consequently a priori analyses are planned at 1 year and 2 years post-completion of TILT (i.e. following the final visit of the final participant) to evaluate overall survival, progression-free survival, adverse events and other long-term clinical outcomes.

## Trial flowchart

See page 10 for the trial flowchart.

**BCG**

**N=4**

Intra-pleural BCG

-

**OK432**

**N=4**

**TILT Trial**

Y

Consent to receive BCG/OK432

**TILT Trial**

-

Y

Intra-pleural OK432

Randomisation

1:1:1

N

**Follow up 2**

Week 6

**Random selection**

Week 0

Week 1

**Intervention**

Week 0-2

Becomes eligible for TILT

N

**Screening**

During cohort visits

**Final visit**

Week 12

**ASSESS-meso cohort**

End of cohort follow up

**Follow up 1**

3 days post intervention (or week 3 for controls)

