# TRIAL FOLLOW UP ASSESSMENTS

## Trial visits

As well as an initial screening visit at Week 0, participants will attend 3 trial assessment visits within the subsequent 12 weeks, with participants in the intervention arm returning for two additional visits; one to receive OK432/BCG within 14 days of randomisation (i.e. days 0-14) and a follow-up safety visit on day 3 post-IMP administration. Trial visits will take place at 3 weeks, 6 weeks and 12 weeks post-randomisation.

Participants who receive an IMP will also be contacted by telephone by a member of the trial team, daily for up to 5 days after IMP administration, to check on their well-being. Trial visits must occur as scheduled +/- 3 days, with the exception of the 3 day post intervention visit which must occur on day 3. Trial procedures and assessments for each visit are detailed in section 9.7. The trial flowchart is shown in section 2.4.

Having completed the 12 week trial period, participants will return to clinical follow up as part of the ASSESS-meso. They will participate in ongoing data collection in accordance with the ASSESS-meso protocol which will continue until death, loss to follow up or withdrawal from ASSESS-meso.

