## Safety assessments

Details of adverse event and serious adverse event reporting are presented in section 12. Adverse events will be assessed on each assessment visit and reported on eCRFs and specific adverse event forms. There is a ‘free text’ section on the adverse event form to allow staff to document any specific adverse event features as reported by patients. As well as usual adverse event reporting, eCRFs will specifically record deaths within the study period and episodes of systemic sepsis or pleural infection.

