## End of trial (EoT)

Trial recruitment will cease in November 2019, regardless of the number of participants enrolled. EoT date, therefore, will be 12 weeks after enrolment of the 12^th^ trial patient or 12 weeks after the recruitment window closes, whichever happens first. At EoT, participants will return to clinical follow up within ASSESS-meso, which will continue until death, loss to follow up or withdrawal from the study. Data from ASSESS-meso will be used to evaluate overall survival at EoT.

|  |  | **Screening**  **Week 0*** | **Intervention**  **Day 0-14** | **3 days post-intervention**  **(Week 3)** | **Week 6** | **Week 12** |
| --- | --- | --- | --- | --- | --- | --- |
| **Clinical assessment** | Assessment of eligibility | X | **X** |  |  |  |
|  | History of pleural interventions | X |  | X | X | X |
|  | Previous oncological treatment | X |  |  |  |  |
|  | Medication history | X | **X** | X | X | X |
|  | WHO/ECOG performance status | X | **X** | X |  |  |
|  | Vital signs, pulse oximetry | X | **X** |  |  |  |
|  | Physical examination | X |  |  |  |  |
|  | Insertion of IPC (if not already in situ) | X |  |  |  |  |
|  | Pleural fluid drainage diary review | X |  | X | X | X |
|  | Documentation of AEs |  | **X** |  | X | X |
| **Blood tests** | Screening blood tests (HIV screen, hepatitis screen, immunoglobulins, random glucose, thyroid function tests) | X |  |  |  |  |
|  | Pregnancy test  (if female <55 yrs) | X |  |  |  |  |
|  | Coagulation panel | X |  |  |  |  |
|  | Trial blood tests (Full blood count, urea & electrolytes, liver function tests, C reactive protein) | X | **X** | X | X | X |
|  | Serum mesothelin | X |  | X | X | X |
|  | Pleural fluid sampling and storage | X | **X** | X | X | X |
|  | Mantoux test (if logistically possible, BCG arm only) | X |  |  |  | X |
| **Randomisation & intervention** | Random selection | X |  |  |  |  |
|  | Informed consent for TILT |  | **X** |  |  |  |
|  | Administration of OK432/BCG |  | **X** |  |  |  |
| **PROMS** | Breathlessness & chest pain VAS score | X |  | X | X | X |
|  | Daily VAS score completion |  |  |  |  |  |
|  | EQ-5D-5L QoL questionnaire | X |  | X | X | X |
| **Radiological imaging** | Chest x-ray | X | **X** | X | X | X |
|  | Thoracic ultrasound | X | **X** | X | X | X |
|  | CT chest (within preceding 2 weeks) | X |  |  |  | X |
| **Qualitative research** | Participant interviews |  |  |  |  | X |
|  | Focus groups with relatives/carers |  |  |  |  | X |

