## Adverse events in TILT and ASSESS-meso participants

Adverse event data is collected at every visit, for all participants in ASSESS-meso and TILT. Whilst participants in ASSESS-meso will not experience any adverse reactions (AR) since they have not received an intervention, it is nonetheless possible that they may experience AEs or SAEs.

Although ASSESS-meso participants are not considered CTIMP participants, some will nonetheless be contributing ‘control’ data to the TILT trial. For clarity and transparency of reporting, all SAEs occurring in ‘control’ participants will be reported to the sponsor in accordance with the specifications below.

Furthermore, because TILT participants will return to follow up in ASSESS-meso following the end of trial, ongoing adverse events monitoring is required in case of any late adverse reactions that present after the 3 month trial period. Reporting of these adverse events will comply with the reporting procedure outlined below. In addition, trial-specific protocol 6b (TSP06b) will contain information on potential adverse reactions to OK432 and BCG, and advice on appropriate management. This TSP will continue to be available for TILT participants once they have returned to ASSESS-meso following the end of trial.

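### The flowchart and visit schedule merge the treated arms' day-3 safety visit with Week 3, contrary to Section 9.1, and the schedule leaves AE documentation unmarked in the merged column

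*Protocol*

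**What the plan says.** **Section 9.1, Trial visits.** The common visits are plain: "Trial visits will take place at 3 weeks, 6 weeks and 12 weeks post-randomisation". The section also has "participants in the intervention arm returning for two additional visits": one for dosing, the other "a follow-up safety visit on day 3 post-IMP administration". Visits carry a window of 3 days either way, except the day-3 visit, which is fixed. For what is done at each visit, Section 9.1 refers the reader to Section 9.7.

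**Section 2.4, flowchart.** Follow up 1 is labelled "3 days post intervention (or week 3 for controls". Only Follow up 2 (Week 6) and the final visit (Week 12) come after it.

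**Section 9.7, schedule of visits.** Between the intervention and Week 6 columns stands one column, headed "3 days post-intervention (Week 3". Breathlessness and pain scores, EQ-5D-5L, serum mesothelin, routine bloods, chest x-ray and ultrasound are all marked in it. The row "Documentation of AEs" is marked at the intervention, Week 6 and Week 12, and is empty in this column.

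**Sections 9.4 and 12.4.** On adverse events the text says "Adverse events will be assessed on each assessment visit" and "Adverse event data is collected at every visit, for all participants in ASSESS-meso and TILT".

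**The concern.** The protocol describes two visit structures for the treated arms. Section 9.1 cannot simply be taken to prevail, because it hands the content of each visit to the table that conflicts with it. A site, or whoever builds the electronic case report forms, could work from the table and never create a Week 3 visit for treated participants.

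Three things depend on this:

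- **Exploratory comparison.** At the first follow-up, treated participants would be measured 3 days after dosing and controls about three weeks after randomisation. Section 13.2 uses the secondary data to choose the full trial's primary outcome and to estimate its variance, so a misaligned visit could carry forward.
- **Feasibility criterion.** Data completeness above 90% is one of the primary criteria (Sections 2.3 and 9.2). Its denominator depends on which visits are expected.
- **Adverse events.** The visit that Section 9.1 names as a safety visit has no adverse event mark in the schedule.

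**Working it through.** **1. Visit count in a treated arm, after screening**

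| Source | Visits | Total |
|---|---|---|
| Section 9.1 | Weeks 3, 6, 12, plus dosing and day 3 | 3 + 2 = 5 |
| Flowchart and schedule | Dosing, day 3, Week 6, Week 12 | 4 |

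The five visits of Section 9.1 cannot be reproduced from the flowchart or the schedule. The missing one is Week 3.

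**2. Timing of the first follow-up if the flowchart or schedule is used**

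Inputs: dosing on days 0 to 14 from random selection (intervention visit section); day-3 visit fixed and other visits within 3 days either way (Section 9.1); time counted from randomisation (section on TILT and ASSESS-meso related activities).

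- Treated: 0 + 3 = day 3, to 14 + 3 = day 17.
- Controls: 21 − 3 = day 18, to 21 + 3 = day 24.
- Gap at nominal days: 21 − 17 = 4, to 21 − 3 = 18 days.
- Gap with the control window: 18 − 17 = 1, to 24 − 3 = 21 days.

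Even the latest permitted dosing day puts the treated visit one day before the control window opens. Under Section 9.1, both groups would be seen on days 18 to 24; at the nominal day 21, treated participants would be 21 − 14 = 7 to 21 − 0 = 21 days past dosing.

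**3. Expected visits and completeness (illustration)**

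Assume 12 participants, all 8 selected accept and are dosed, there are no deaths, and completeness is counted by visit. The protocol does not fix the counting unit.

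- Section 9.1: 8 × 5 + 4 × 3 = 52 post-screening visits.
- Schedule: 8 × 4 + 4 × 3 = 44.
- If sites follow the schedule but completeness is counted against Section 9.1, the ceiling is 44/52 = 84.6%. Adding the 12 screening visits to both gives 56/64 = 87.5%.

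On these assumptions, the mismatch alone would put the trial below 90%. Counting by data item would give other figures.

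**4. Adverse event row**

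| Screening | Intervention | Day 3 / Week 3 | Week 6 | Week 12 |
|---|---|---|---|---|
| blank | marked | blank | marked | marked |

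On the table alone, the next mark after dosing is Week 6: 42 − 14 = 28 to 42 − 0 = 42 days later at nominal days, or 39 − 14 = 25 to 45 − 0 = 45 days with the window. This describes the table, not what the whole protocol requires. The empty column contradicts Sections 9.4 and 12.4, for controls at Week 3 as well as for treated participants at day 3.

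**The case against.** The other side has a good case on consequences, less so on the contradiction.

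**Adverse events.** A reader might infer from the empty cell that acute reactions would go unrecorded. The protocol does not support that. Section 12.1 requires every adverse event to be entered on the case report form and in the notes. Section 12.2 extends this to all reactions, expected ones included. Section 12.5 puts non-serious reactions on a log as well. The dosing visit has its own mark, and treated participants are telephoned daily for up to 5 days. This objection stands and limits the point to a risk of omission.

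**Bias.** A reader might also infer that the arms will be compared at different times and that this biases against the agents. The mistiming arises only if sites follow the flowchart or schedule instead of Section 9.1. No secondary outcome is defined specifically at Follow up 1; tumour response and progression-free survival are read at 12 weeks. Repeated measures are modelled with adjustment for baseline, and Section 9.3 has symptom scores and questionnaires completed daily for part of Weeks 0 to 3. No time of peak reaction is given, and no direction of effect is shown for mesothelin. The 23% fever and 15% injection-site figures for OK432 are not specific to intra-pleural use and give no timing, so they do not measure what day 3 would show or miss.

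**Text extraction.** The table was read by a program, and its daily symptom-score row is wholly blank although daily completion is planned, so marks may have been lost. The adverse event row kept its other three marks, so its gap is more likely real, but it should be checked against the original. The merger of visits does not rest on that cell: the flowchart states it in words.

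**Conclusion.** The protocol contradicts itself on visit structure. Section 9.1 gives treated participants five post-screening visits; the flowchart and schedule give four, with no Week 3 visit.

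If the flowchart or schedule is followed, the first follow-up falls on days 3 to 17 in treated arms and days 18 to 24 in controls. That exploratory comparison would then mix time from randomisation with the early period after dosing. The set of visits counted for completeness also changes. The blank adverse event cell is a second contradiction, with a risk of omission if forms are built from the table.

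The conclusion rests on the dosing window and visit windows as stated and, for the adverse event cell, on the table having been read correctly. It does not extend to lost safety data or to a demonstrated bias against either agent. The affected outcomes are exploratory, with 4 participants per arm. This is a moderate schedule correction.

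**What to change.** Reconcile the flowchart (Section 2.4) and the schedule (Section 9.7) with Sections 9.1, 9.4 and 12.4:

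- Show the day-3 safety visit (treated participants) and the Week 3 visit consistently in all three places, with separate schedule columns if Section 9.1 is the intended structure, and state which assessments belong to each.
- Mark adverse event documentation at every visit, as the text already requires.
- Compare arms only at visits timed alike from randomisation in all arms.
- Count data completeness against the same reconciled list of visits.

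The cost is an edit to one table and one figure, with a check that the electronic forms match. It adds no visit beyond those in Section 9.1.
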